### Epigenetic Analyses

To explore the association between the methylation pattern of cytosine phosphate guanine (CpG) islands in the regulatory regions of determined genes and main outcomes (ie, obesity, cardiovascular diseases), we will examine the methylation alterations in the CpG regions of determined genes among TCGS participants using methylation-specific polymerase chain reaction, bisulfite-sequencing polymerase chain reaction, and epigenome-wide analysis techniques. Identifying epigenetic modifications associated with cardiometabolic risk factors, including DNA methylation variation, may point to genomic pathways that are dysregulated in numerous conditions. The Illumina Bead Chip array will be use to assay DNA methylation in leukocyte DNA obtained from TCGS participants. Mixed-effects regression models will be used to test the association of methylation beta value with cardiometabolic risk factor changes, adjusting for batch effects and potential confounders. Association analyses of the DNA methylation patterns and TCGS phenotypes will subsequently be performed.

### Sample Size and Power

Sample size and power calculation were estimated according to the TLGS [14] criteria, with the total TCGS duration of 20 years. Due to the wide scope of the project and variety of measured variables, different types of analyses will be performed, depending on the type of report, or the variables and outcomes. Continuous data will be expressed as their measures of location and spread in total, and in subgroups. For qualitative and categorized continuous variables, percentages and frequency distributions will be reported.

Normality of distribution of the continuous variables will be examined using histograms, measures of skewness and kurtosis, Kolmogrove-Smirnove tests, and Chi-square tests. When log-transformed values are used, geometric means will be computed. Percentiles will be used to describe the high or low values of the skewed variables. When assumptions of the parametric statistical methods are not met, nonparametric methods of their counterparts will be used. These methods will also be used for analyses of variables that are not originally continuous, such as attitudes or quality of life.

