### Genetic Association

The present study aims to genotype TLGS participants. Genotyping will be based on a standard SNP array platform suitable for performing a GWAS comprising tag SNPs from all three HapMap phases, and has been strategically selected to capture the greatest amount of common variation and drive the discovery of novel associations with traits and diseases. Incidence rates of cardiometabolic risk factors (ie, diabetes mellitus, angina pectoris, myocardial infarction, hypertension) will be estimated, and adjusted for age and sex. Other variables, such as education level, physical activity, smoking habits, nutritional habits, and drug use will be use as covariables. Relative risks for different factors and their 95% CIs will be reported. Longitudinal linkage analyses will be performed for families, and selected genetic regions will be examining via association analyses. By using common genetic polymorphisms with well-understood effects on exposure patterns, a causal effect from observational data in the presence of confounding factors will be estimated by Mendelian randomization. The most important phenotypes in this project are cardiometabolic risk factors, including diabetes, cardiovascular disease, obesity, and metabolic syndrome. All phenotypes will be analyzed using a case-control and familial based design, and the related genetic regions will be analyzed and replicated in other populations. An Iranian reference panel will be designed and imputed based on a reference panel that will be performed to obtain information about a higher number of variants.

Multifactoriality is expected to play a pivotal role, and this study is currently focused on collecting information on the genetic and environmental factors that potentially influence cardiometabolic diseases. For the gene-gene and gene-environment interaction analyses, it will be assumed that genetics may influence disease risk either directly or via environment effects. The genetic loci can have either independent or epistatic effects, so the model will be a multilogistic model. However, if nonparametric gene-gene interaction is desired, semiparametric regression and least square kernel machines will be used occasionally.

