### Genotype Quality Control Analysis

PLINK program (V 1.07) and R statistic (V 3.2) were used for quality control procedures. 13,894 samples were arrayed, consisting of 6274 males and 7614 females, with the total genotyping rate of 0.9774.

To increase the power of the analyses, some markers (and some samples) were removed from TCGS database after quality control [17]. In the first step of sample quality control, individuals with discordant sex information were identified. In total, 15,031 X chromosome variants were detected in 397 samples, which were removed from analyses. To evaluate heterozygosity among genotyped samples, plots were drawn and the observed heterozygosity rate per individual was examined to decide reasonable thresholds for excluding individuals based on elevated missing heterozygosity or extreme heterozygosity (Multimedia Appendix 5). In this step, 243 individuals were excluded with a genotype failure rate (>0.03) and/or heterozygosity rate >3 standard deviations from the mean. To eliminate the genetic influence of sample contamination, duplications and cryptic first-degree relative sibling pairs, genome-wide average identity by state (IBS)/identity by descent (IBD) values were calculated for each pair of individuals in the present GWAS data set using pruned SNPs (649,932). To check kinship relationships, IBDs were calculated and all relationships were confirmed.

To find individuals with large-scale differences in ancestry, a principal component analysis was conducted and 47 subjects were removed (Multimedia Appendix 6). For marker quality control, those with a minor allele frequency less than 0.01 (n=24,860) and genotype failure rate less than 0.95 (n=2620) were removed. After excluding markers that did not satisfy the Hardy Weinberg Equilibrium (n=14,032, *P*<.001), 608,420 remained for analyses. Multimedia Appendix 7 shows the distribution of SNP call rate after the cleaning process. In summary, the clean data set included 13,399 individuals consisting of 5977 males and 7422 females, with 608,420 markers and a total genotyping rate of 0.9854.

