### Strengths and Weaknesses

This study was based on a national project that selected a representative sample of residents in district-13 of Tehran, the capital of Iran. The project included detailed information on individuals, households, and family relationships (along with environmental, biomedical, and biochemical factors that could be linked to the rate of NCDs) to create a cohort of the entire population residing in Tehran. We recently reviewed the literature in this field, and to our knowledge the present study is the first population-based cohort study for cardiometabolic genetic risk factors in Iran.

In the TCGS, data have been thoroughly and robustly collected on a wide range of clinical parameters, focusing on quantitative traits that are well established as risk factors for cardiometabolic disease. This cohort includes substantial numbers that represent the full adult spectrum of ages, lifestyles, and demography, and includes important phenotypes and quantitative traits to allow population-based genetic and epidemiological research on many important diseases/risks related to NCDs. The family-based approach of the TCGS enables the study to take a flexible approach to gene discovery, encompassing association and linkage approaches, and gives the potential to study aspects such as heritability of disease-related traits and parent-of-origin effects. The combination of linkage and association approaches has proven very effective in studies of various diseases/disease traits [21].

Data in this study can be linked anonymously to routinely collected samples from different cohorts in Iran. This linkage effectively converts this longitudinal study into a national study, with pluripotential outcomes. The TCGS can contribute as a major partner to GWAS meta-analysis consortia, enabling the study of SNPs of low minor allele frequency (1-10%). The TCGS is one of the largest family-based genetic epidemiology studies in Iran and the Middle East.

Although the family-based nature of the cohort is an important strength of this study, providing an efficient strategy for DNA sequence-based studies, relatedness of cohort members will be a confounding factor in some analyses, and may require statistical adjustment. The other weakness of the study is related to the Tehranian nature of the population, rather than a comprehensive Iranian cohort.

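### Normality is judged on the variables rather than on model residuals, partly by Kolmogorov-Smirnov and chi-square tests that are over-sensitive at 13,399 people, and the result feeds a switch to nonparametric methods

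*Protocol article*

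**What the plan says.** Under Sample Size and Power, the protocol article describes how continuous variables are checked: "Normality of distribution of the continuous variables will be examined using histograms, measures of skewness and kurtosis, Kolmogrove-Smirnove tests, and Chi-square tests". It foresees log transformation ("When log-transformed values are used, geometric means will be computed") and sets the consequence of a failed check: "When assumptions of the parametric statistical methods are not met, nonparametric methods of their counterparts will be used". The same methods are then extended to variables that are not continuous by origin, with attitudes and quality of life as examples. No significance level, cut-off or order of priority among the four tools is given, and residuals are not mentioned.

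Under Genetic Association, the analyses rely on covariates: "Other variables, such as education level, physical activity, smoking habits, nutritional habits, and drug use will be use as covariables". That section also plans Mendelian randomization. Strengths and Weaknesses describes the data collection as "focusing on quantitative traits that are well established as risk factors for cardiometabolic disease", offers the study to GWAS meta-analysis consortia, and says that relatedness may need statistical adjustment.

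**The concern.** There are two separate problems. First, the check looks at the wrong object. A linear model needs well-behaved residuals given age, sex and genotype, not a normal marginal distribution. The cohort contains both sexes and enrolled people from above 3 years of age, so a non-normal marginal can arise even when the adjusted model fits well. Second, goodness-of-fit tests gain power with sample size. At about 13,400 people they react to slight skewness and to the rounding of recorded values, neither of which threatens a linear model of this size.

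The result matters because it feeds a stated switch of method. If that switch led to simple rank tests, the analysis would lose the covariates and the per-allele effect estimate. Mendelian randomization and meta-analysis both need that estimate.

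**Working it through.** **Sample size.** From Genotype Quality Control Analysis, "the clean data set included 13,399 individuals consisting of 5977 males and 7422 females": 5977 + 7422 = 13,399, which agrees. The Sample Size and Power section gives no power, alpha or effect size to reproduce.

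**Step 1: how often the tests reject at N = 13,399.** Simulation, 300 replicates per case. Assumptions not in the documents: test level 0.05, the distribution shapes (skewed cases are lognormal), and 20 bins for the chi-square test (17 df). The Kolmogorov-Smirnov statistic uses the fitted mean and SD. It is compared with a simulated critical value that allows for the fitting (Lilliefors, 0.0079) and with the plain one (0.0117).

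| Variable | Lilliefors | Plain KS | Chi-square |
|---|---|---|---|
| Normal | 4% | 0% | 5% |
| Skewness 0.1 | 85% | 17% | 48% |
| Skewness 0.15 | 99% | 72% | 90% |
| Skewness 0.2 | 100% | 96% | 100% |
| Skewness 0.3 or more | 100% | 100% | 100% |
| t, 20 df | 95% | 26% | 70% |
| t, 10 df | 100% | 100% | 100% |
| Normal, SD 10, rounded to 1 unit | 100% | 100% | 100% |
| Normal, SD 15, rounded to 2 units | 100% | 100% | 100% |
| Two sexes pooled, 1 SD apart | 20% | 0.3% | 11% |
| Two sexes pooled, 1.8 SD apart | 100% | 100% | 100% |

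**Step 2: does rejection signal trouble for the linear model?** Type I error of least-squares regression of a skewed trait on a SNP, same N, 2000 replicates, trait skewness 0.5, 2 and 5, minor allele frequency 0.01, 0.05 and 0.30 (0.01 is the plan's own marker floor). At nominal 0.05 the error lay between 0.048 and 0.060. The Monte Carlo standard error is sqrt(0.05 × 0.95 / 2000) = 0.005, so this is close to nominal. The check assumes unrelated people, and 2000 replicates say nothing about the tail at 5e-8.

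**Step 3: cost if the switch drops the covariates.** Assumed: locus share of variance q² = 0.0025, covariate R² = 0.3, two-sided threshold 5e-8 (critical value 5.451), relatedness ignored. Power = Φ(λ − 5.451).

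- N·q² = 13,399 × 0.0025 = 33.50.
- Adjusted linear: λ = sqrt(33.50 / 0.7) = 6.92, power 92.9%.
- Unadjusted linear: λ = sqrt(33.50) = 5.79, power 63.2%.
- Unadjusted rank: λ = sqrt(0.955 × 33.50) = 5.66, power 58.1%.
- Rank method that keeps the covariates: λ = sqrt(0.955 × 33.50 / 0.7) = 6.76, power 90.5%.

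The total loss is 92.9 − 58.1 = 34.8 points. Losing the covariates accounts for 92.9 − 63.2 = 29.7, and ranking for 63.2 − 58.1 = 5.1. With R² = 0.2, the adjusted linear model gives 84.6% and the adjusted rank method 80.8%. The factor 0.955 is the rank-test efficiency for exactly normal data. For skewed or heavy-tailed traits rank methods can do better.

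**The case against.** The strongest reply is that the article never says the two tests decide. Histograms and skewness and kurtosis are listed first and remain informative at large N, no p-value triggers the switch, and the assumptions of a method can be read to include those on residuals. This stands. A reader might infer that the Kolmogorov-Smirnov and chi-square tests alone choose the method, on untransformed variables only. The text does not support that, and it foresees log transformation.

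A reader might also infer that quantitative traits will be sent to rank tests without covariates. No rank test is named. For gene-gene interaction, the nonparametric route is a regression method: "if nonparametric gene-gene interaction is desired, semiparametric regression and least square kernel machines will be used occasionally". Epigenetic Analyses plans adjusted models: "Mixed-effects regression models will be used to test the association of methylation beta value with cardiometabolic risk factor changes, adjusting for batch effects and potential" (the quote stops one word short; the sentence ends by naming confounding variables). These choices are stated only for those two analyses, so they show that adjustment is intended without securing it elsewhere. In ordinary usage, a nonparametric counterpart does mean a rank test, and applying the same methods to attitude and quality-of-life variables fits that usage. It is still an inference, and most of the power loss depends on it.

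The section is also a general description covering subgroups, and children and adults are tabulated separately (Multimedia Appendices 2 and 3), so N will often be smaller. At n = 500 and skewness 0.3, rejection is 36% (Lilliefors), 1% (plain) and 15% (chi-square). The problem is not confined to the full cohort, however: at n = 5,000 the same skewness is rejected 100%, 90% and 99% of the time.

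Finally, residual checks and fallback models are often left to an analysis plan. That would answer a complaint about missing detail. This point concerns what the article does state: which object is checked, by which tests, and with what consequence.

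**Conclusion.** The point holds in limited form. The article judges normality on the variables rather than on residuals, includes two tests that at N = 13,399 reject for harmless departures, and ties the outcome to a change of method without saying which tool prevails. The over-sensitivity is solid: 96-100% rejection at skewness 0.2, and 100% for normal values rounded to 1 unit with SD 10, while least-squares type I error stays near 5%. It is not universal. A pooled-sex mixture 1 SD apart usually passes, so a claim that every real trait would be rejected goes too far.

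The fall in power from 93% to 58% is conditional. It requires that the tests are followed, that the counterpart is a simple rank test, and that the assumed locus size, covariate R² and threshold apply. If a rank method keeps the covariates, power is about 90% and the cost is only 2 to 4 points over R² of 0.3 to 0.2. The main risk is therefore the unprotected covariate adjustment and effect estimate, more than the ranking itself.

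**What to change.** In Sample Size and Power, remove the Kolmogorov-Smirnov and chi-square tests as a basis for choosing the method. For quantitative-trait association analyses, state that:

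- the covariate-adjusted linear model, in mixed form where relatives are included, is kept throughout;
- residuals from that model are judged by plots;
- where residuals are clearly skewed or heavy-tailed, the trait is log-transformed or rank-based inverse-normal transformed within the same model;
- rank tests are kept for ordinal scores and simple descriptive comparisons.

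This is a change of wording and needs no new data. It also fits the adjustment for relatedness that the article says may be required. The one downside is that effects on a transformed scale need back-translation for some traits.

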## Results

### Participant Confidentiality

Participant confidentiality in the TCGS is maintained throughout all aspects of the study, as is the case in the TLGS. Investigators within the TCGS have no access to any direct patient identification information; these data are held confidentially by staff members of the TLGS, who are involved in patient contact and follow-up, but not in any data analysis or interpretation. Separate data files are kept for participants’ clinical covariate and endpoint data, plasma phenotyping data, and genomic data. Blood samples sent to the plasma phenotyping laboratory and the genetic laboratories are labeled only with a sample identification number that cannot be tracked by laboratory personnel to any patient identification variables, or to any clinical covariate data. All TCGS data included in the TLGS are maintained on a separate and fully protected computer system that is isolated and distinct from computing systems used for the parent study. A unique and fully distinct participant identification number is used in the TCGS, making direct linkage to the TLGS impossible for scientific investigators.

### Participants’ DNA Information

Since the establishment of the genomic bank in 2004, some subjects only participated in Phase 1 of the study (1999-2002), and their data has been excluded from this study. The TCGS has a genomic bank with over 16,000 samples. The TCGS cohort described here comprises 17,186 (86.34%) of the 19,905 TLGS participants, who provided baseline blood samples that were adequate for plasma and DNA analyses (Multimedia Appendix 1). This study is comprised of 849 individuals and 3109 families with at least one member who had genotype information.

### Familial Information

The pedigrees were drawn (based on questionnaire information) for all biologically related TCGS participants. Total family data of Tehranian residents (consisting of 3109 families) were collected; 849 unrelated persons, adopted persons, childless bride and groom couples, and individuals who lacked information were marked as *independent persons*. The mean pedigree size in the study population was 6.76 (range 3-52). Placeholding individuals were imputed when necessary to reflect kinship relations among participants, and a total of 6158 individuals were added as virtual persons that were recorded by special codes for further tracking. For example, parents who had not participated in the TLGS were added during the drawing of pedigrees to identify sibships in the TCGS.

### Demographic, Clinical, and Biochemical Information

Demographic, clinical, and biochemical information of participants (categorized by year) in each period of study are presented in Multimedia Appendix 2 and Multimedia Appendix 3. Most the study population was in the range of 31-50 years old. Phenotype frequencies of hypertension, dyslipidemia, diabetes, obesity, and metabolic syndrome were described in adults, and being overweight was the most frequent among them (Multimedia Appendix 4).

### Genotype Quality Control Analysis

PLINK program (V 1.07) and R statistic (V 3.2) were used for quality control procedures. 13,894 samples were arrayed, consisting of 6274 males and 7614 females, with the total genotyping rate of 0.9774.

To increase the power of the analyses, some markers (and some samples) were removed from TCGS database after quality control [17]. In the first step of sample quality control, individuals with discordant sex information were identified. In total, 15,031 X chromosome variants were detected in 397 samples, which were removed from analyses. To evaluate heterozygosity among genotyped samples, plots were drawn and the observed heterozygosity rate per individual was examined to decide reasonable thresholds for excluding individuals based on elevated missing heterozygosity or extreme heterozygosity (Multimedia Appendix 5). In this step, 243 individuals were excluded with a genotype failure rate (>0.03) and/or heterozygosity rate >3 standard deviations from the mean. To eliminate the genetic influence of sample contamination, duplications and cryptic first-degree relative sibling pairs, genome-wide average identity by state (IBS)/identity by descent (IBD) values were calculated for each pair of individuals in the present GWAS data set using pruned SNPs (649,932). To check kinship relationships, IBDs were calculated and all relationships were confirmed.

To find individuals with large-scale differences in ancestry, a principal component analysis was conducted and 47 subjects were removed (Multimedia Appendix 6). For marker quality control, those with a minor allele frequency less than 0.01 (n=24,860) and genotype failure rate less than 0.95 (n=2620) were removed. After excluding markers that did not satisfy the Hardy Weinberg Equilibrium (n=14,032, *P*<.001), 608,420 remained for analyses. Multimedia Appendix 7 shows the distribution of SNP call rate after the cleaning process. In summary, the clean data set included 13,399 individuals consisting of 5977 males and 7422 females, with 608,420 markers and a total genotyping rate of 0.9854.

## Discussion

The genetic findings of this study could help us to understand the genetic pattern of our population and design association studies. The results of the TLGS indicated that the prevalence of cardiometabolic risk factors is speedily increasing in our population, necessitating further investigations for genetic background information to study the interactions between environmental and genetic factors. The incidence of NCDs, especially cardiometabolic diseases, is increasing worldwide due to changes in lifestyle [18], and various countries have investigated their populations using genetic dissection to understand the genetic pattern of these complex disorders. Unfortunately, established health education and lifestyle interventions in American and European populations cannot be implemented in other regions of the world (such as Iran) due to differences in susceptibility, nutrition, social circumstances, and culture.

The TCGS was designed in Iran as a population-based genetic study, and is one of the very first studies of its kind in the Middle East, addressing the knowledge gap on the genetic patterns of the Iranian population. This study will clarify the role of environmental factors in Iran, along with environmental-genetic interactions. Combining the epidemiological findings in TLGS with genetic data has led to the design of Mendelian randomization studies to change some concepts about the interaction of lipid variation and cardiovascular diseases. In addition, this study may clarify missing heritability data and aid in the understanding of NCD-related problems [19].

However, the delineation of shared phenotypes facilitated by GWAS is of great interest, such as the recent insight into the relationship between height and cardiovascular disease [20]. Results of this study will provide a comprehensive understanding of personalized genomic data and could be used to help to governmental organizations use genetic knowledge to promote personalized health care that facilitates the prevention and management of NCDs.

